## Abstract

**Introduction:**

Systemic Sclerosis (SSc) is associated with substantial disability in affected patients. Although exercise interventions for SSc have been developed, most focus on isolated body segments rather than global disability. Thus, this study aims to assess the feasibility of a functional activity‐based exercise programme designed to address disability in individuals with SSc.

**Methods:**

This feasibility study protocol is designed as a randomised controlled mixed‐methods trial. It will include individuals with SSc aged 18–65 years and with a score ≥ 1 on the Scleroderma Health Assessment Questionnaire (SHAQ). Participants will be randomly allocated to either a control group, receiving an educational booklet on the disease, or an intervention group receiving the booklet plus a 10‐week supervised functional exercise protocol (twice weekly). Feasibility outcomes include recruitment and retention rates, adherence, safety, and adverse events. Preliminary clinical outcomes will address disability level, physical function, fatigue, resilience, symptoms of anxiety and depression, and perceived change. Quantitative data will be analysed using descriptive and inferential statistics, while qualitative data will undergo thematic content analysis.

**Ethical Approval:**

The study was approved by the Institutional Ethics Committee (Approval Number: 6.992.710).

**Results:**

The study is in its initial phase. The reference clinic has 219 registered patients, of whom 183 (83.6%) are preliminarily eligible. Recruitment and subsequent feasibility results are ongoing.

**Conclusion:**

This protocol proposes an innovative and low‐cost approach, whose results will support refinements for a more rigorous clinical trial, despite potential logistical and disease‐related limitations.

## Introduction

1

Systemic sclerosis (SSc) is a chronic multisystem disease that is associated with significant disability (Zaghlol et al. 2022). The International Classification of Functioning, Disability and Health (ICF) defines disability as the difficulty an individual experiences in performing daily activities or participating in society (Organização Mundial da Saúde 2008). In SSc, disability can be attributed to the cumulative impact of multiple impairments caused by or associated with the disease (Jaeger et al. 2018; Khanna et al. 2017; Papelard et al. 2019; Yetisir et al. 2025).

The management of SSc is based on continuous assessment to address potential complications, with the implementation of both pharmacological and non‐pharmacological strategies (Thoreau et al. 2021). Patient education and physical exercise are the most studied non‐pharmacological approaches. However, most exercise protocols focus on specific body segments, such as hand function (Bongi et al. 2011; Piga et al. 2014; Santos Cardozo Roque et al. 2022).

The ICF *core set* developed for SSc patients identified significant limitations in global functions within the *activity and participation* domain. These include daily routines, postural changes, object manipulation, walking, household tasks, and leisure activities (Papelard et al. 2019). These findings reinforce the need for exercise therapies that address more than isolated body segments.

Thus, we hypothesise that a functional activity–based exercise programme reduces the disability in individuals with SSc, thereby improving perceived quality of life and reducing the disease's impact on patients' lives. Accordingly, the objective of the future randomised controlled trial (RCT) will be to evaluate the effect of a functional activity–based exercise programme on functionality in individuals with SSc compared to a control group.

However, prior to conducting a RCT, a feasibility study will be performed to assess the viability of the proposed methodology and intervention protocol. This step allows for necessary adjustments before proceeding with the full trial. Therefore, the objective of this study is to assess feasibility‐related outcomes, including recruitment, retention, the acceptability, adherence and safety of the intervention, as well as to report on intervention costs, and the occurrence of any adverse events.

## Methods

2

### Design and Setting

2.1

This study protocol describes a mixed‐methods randomised controlled feasibility study. To be conducted at the rheumatology outpatient clinic of the Hospital das Clínicas at the Federal University of Pernambuco (HC‐UFPE) (a reference centre for SSc care in the state of Pernambuco) and at the Laboratório de Aprendizagem e Controle Motor (LACOM).

### Participants

2.2

The study includes individuals aged 18–65 years, of any sex, with a score ≥ 1 on the *Scleroderma Health Assessment Questionnaire* and a diagnosis of SSc based on the 2013 classification criteria from the American College of Rheumatology/European League Against Rheumatism (van den Hoogen et al. 2013).

Exclusion criteria are: pregnancy; active malignancy; recent (3 months) changes in pharmacotherapy; physical therapy treatment in the past 3 months; overlap with other autoimmune rheumatic diseases that primarily affect the musculoskeletal system; presence of conditions that limit physical activity (e.g., severe neurological impairment, immobility or advanced cardiopulmonary symptoms); individuals who engage in regular physical exercise (at least three times per week); cardiac symptoms classified as class III or IV according to the New York Heart Association (Caraballo et al. 2019); and joint surgery within 6 months prior to study inclusion. Eligibility was determined through clinical assessment.

### Procedure: Screening, Informed Consent, Randomisation, Allocation Concealment, and Blinding

2.3

The researcher will recruit patients directly in the HC‐UFPE waiting room. When inviting participation, the study procedures are explained, and if interest is shown, a preliminary eligibility check is conducted based on self‐reported information and clinical records to verify inclusion and exclusion criteria. The reasons for including or excluding each individual are recorded.

If the individual is eligible and agrees to participate, they receive the Informed Consent Form (ICF) for review and signature. No research‐related assessments, data collection, or intervention procedures were initiated prior to the signing of the informed consent.

After consent is obtained, participants are randomised into one of the two study groups. Randomisation uses block allocation (*n* = 10) via sealed opaque envelopes. Envelopes are opened only after the participant's baseline assessment.

Data collection was performed by Examiner A or B, both of whom were blinded to group allocation. Participants are instructed not to disclose to researchers A and B the group to which they were allocated. The exercise protocol was administered by Examiner C, who will be the only one aware of the participants' group assignments.

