### Feasibility Assessment

3.1

To assess the feasibility of the study, the following data will be collected (Pearson et al. 2020):Eligibility rate: the percentage of patients registered at the outpatient clinic who were eligible for recruitment;Recruitment rate: the proportion of eligible individuals who agree to participate. The number of participants recruited per month will also be estimated;Randomisation rate: the proportion of recruited participants who were successfully randomised;Retention rate: the proportion of participants who completed all planned assessments. A rate of 70% will be considered adequate (Teresi et al. 2022);Adherence rate: the proportion of participants who completed the entire protocol;Protocol fidelity: documented by recording any unplanned adaptations, including their reasons and types;Acceptability: assessed through participants' self‐reported difficulties or discomfort related to the protocol and the study. These reports will be collected as notes during each session. Acceptability will also be explored through qualitative data from semi‐structured interviews, focusing on participants' opinions and challenges during protocol implementation.

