## Results

4

The intervention protocol was registered with the Brazilian Registry of Clinical Trials (ReBEC) under the code RBR‐10nbcsbw. The study is currently in its initial phase.

In collaboration with healthcare professionals from the rheumatology outpatient clinic at HC‐UFPE, a survey was conducted to determine the total number of patients registered as receiving care. The number of patients preliminarily eligible for research participation was then assessed. The outpatient clinic currently has 219 patients under care. Of these, 183 are eligible for the present research.

The next phase of the research will involve the initiation of screening procedures. Screening will be conducted weekly on Wednesdays, when the outpatient clinic provides care for patients with SSc. On average, 11 patients are scheduled per day. The principal researcher will approach potential participants in the waiting room.

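### The recruitment rate has no named denominator, and neither of the two the plan allows measures willingness among the eligible patients approached

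*Protocol article*

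**What the plan says.** Four parts of the protocol article bear on this point.

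- **Order of steps (section 2.3).** The researcher invites the patient and explains the study, "and if interest is shown, a preliminary eligibility check is conducted", drawing on what the patient reports and on the clinic's records. Consent follows for those who are eligible and agree. The section adds: "The reasons for including or excluding each individual are recorded".
- **Recruitment rate (section 3.1).** It is defined as "the proportion of eligible individuals who agree to participate". A monthly count of recruits is also planned.
- **Eligibility rate (section 3.1, the item before).** It is defined as "the percentage of patients registered at the outpatient clinic who were eligible for recruitment".
- **Clinic count (section 4, Results).** "The outpatient clinic currently has 219 patients under care. Of these, 183 are eligible for the present research". The same section and the Abstract call this eligibility preliminary. Screening is the next phase, on Wednesdays, with about 11 patients scheduled per day: "The principal researcher will approach potential participants in the waiting room".

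The recruitment target is 12 per group (section 3.4).

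**The concern.** Recruitment comes first in the list of feasibility outcomes in the Introduction, and the study exists so that the methods can be adjusted before a full trial. For that purpose the useful figure is the share of eligible patients approached who consent.

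Under the order in section 2.3, a patient who declines at the invitation gets no eligibility check at that visit. If the recruitment rate rests on that check, such a patient is in neither numerator nor denominator. The rate then describes how often interested patients go on to sign, and could look high even if most eligible patients had refused.

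This cannot safely be left to the analysis. If a decliner's current eligibility is not established at the approach, it is hard to recover later.

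**Working it through.** **Inputs from the article**
- Registered patients: 219. Preliminarily eligible: 183 (section 4).
- Target: 12 per group in two groups, so 2 × 12 = 24 (section 3.4).
- Interest share and refusal rate: not given.

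**The article's own figure.** 183/219 = 0.8356, or 83.6%, which matches the Abstract.

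**Definitions**
- i = share of eligible approached patients who show interest (assumed).
- c = share of interested eligible patients who consent (assumed 0.9).
- Rate wanted, over eligible patients approached: i × c.
- Reading A, denominator = those found eligible at the waiting-room check: (i × c)/i = c.
- Inflation under reading A: c/(i × c) = 1/i, whatever the value of c.
- Reading B, denominator = the clinic count: 24/183 = 13.1% at full target, whatever i and c are.
- Eligible patients approached to reach the target: 24/(i × c).

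| i (assumed) | Rate wanted, i × 0.9 | Reading A | Inflation, 1/i | Eligible approached, 24/(i × 0.9) | Reading B |
|---|---|---|---|---|---|
| 0.3 | 27% | 90% | 3.33 | 88.9 | 13.1% |
| 0.5 | 45% | 90% | 2.00 | 53.3 | 13.1% |
| 0.7 | 63% | 90% | 1.43 | 38.1 | 13.1% |
| 0.9 | 81% | 90% | 1.11 | 29.6 | 13.1% |

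In every row the target is reached before 183 eligible patients have been approached. Reading B therefore counts as non-recruits many patients who were never asked. At i = 0.5, for example, 53.3 of 183 are approached (29.1%), and 0.291 × 45% = 13.1%.

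Neither reading responds to i: A stays at c and B stays at 24/183. The interest share, which is what differs between a clinic where most patients accept and one where most refuse, affects neither figure.

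**Which reading does the text favour?** The consent step in section 2.3 pairs being eligible with agreeing, directly after the waiting-room check. The definition in section 3.1 uses the same pairing, which points to A. In section 3.1, however, the recruitment rate directly follows an eligibility rate defined over the whole clinic, which points to B. The article does not settle it.

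**The case against.** The strongest reply is that the clinic-wide count was made before screening and regardless of interest. A patient who declines at first approach can be among the 183. A reader might infer from section 2.3 that only willing patients ever have their eligibility assessed, and hence that the recruitment rate is certain to be biased upward. The article does not support that inference: the bias arises only under reading A, and no sentence adopts that reading.

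This part of the reply stands, but reading B does not repair the measure. The 183 are only preliminarily eligible. Several criteria in section 2.2 change over time or depend on what the patient reports: the SHAQ score, recent drug changes or physiotherapy, and regular exercise. The article does not show that the survey applied them all. The target also limits the resulting rate, as shown above.

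The other replies have partial force:
- **Reasons are recorded for each individual.** The sentence does not exclude early refusals, but it follows the eligibility check and does not expressly cover them. A logged refusal without an eligibility status still cannot be placed in a denominator of eligible people.
- **The approach may be limited to patients already identified as preliminarily eligible.** Section 4 is compatible with this but does not say so.
- **The monthly count is usable for planning and does not depend on the denominator.** This is true, and it limits the damage. It does not separate patient flow from willingness, however.
- **No progression threshold depends on the recruitment rate.** This is also true. In section 3.1 only retention has one.
- **A condensed article may omit screening-log detail.** This is accepted for the log. The order of invitation and check, however, is stated, and it decides what can be known about decliners.

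**Conclusion.** The point holds as a problem with an unnamed denominator. Sections 2.3, 3.1 and 4 allow two denominators, and neither gives the share of eligible approached patients who consent.

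- **Waiting-room check as denominator:** the rate is inflated by 1/i. The factors of 1.1 to 3.3 rest on assumed interest shares of 90% down to 30%. The actual size cannot be computed from the article.
- **Clinic count as denominator:** the rate is at most 13.1% if recruitment stops at 24, and it understates willingness wherever a sizeable part of the 183 is never approached.

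The change should be made before screening starts. A main feasibility figure is at risk; participant safety is not.

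**What to change.** **Section 2.3.** Check each Wednesday's list (about 11 patients) against the criteria that records can settle before anyone is approached, as far as ethics approval allows. Log every patient approached, including those who refuse before the eligibility check, with reasons where given.

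**Section 3.1.** Define the recruitment rate as consented divided by record-eligible patients approached. If records cannot be checked first, use all patients approached. State that criteria resting on self-report or on the SHAQ are settled only after interest is shown, so record-eligible is still a provisional status.

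**Reporting.** Give five counts separately: approached, record-eligible, declined before the check, declined after it, and consented. Interest-to-consent conversion and the monthly count can then stand beside the rate without being confused with it.

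**Cost.** About one added sentence in each of the two sections, and a few minutes of record checking per clinic day using records the procedure already consults. The reported rate will be lower than under reading A. Ethics approval may limit the record check before the approach, which is why the all-approached denominator is kept as a fallback.

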### Study Groups

2.4

Control group (CG): Participants receive an educational booklet on SSc developed by the Brazilian Society of Rheumatology (Sociedade Brasileira de Reumatologia and Comissão de Esclerose Sistêmica 2025). For those with reading difficulties, a research member will provide a video explanation via WhatsApp. Additionally, participants are instructed not to begin any physiotherapeutic intervention or exercise practice that could affect their physical conditioning during the study. After the final assessment, participants in this group will be offered follow‐up care using the study's intervention protocol.

Functional exercise group (FEG): In addition to receiving the same booklet (or video) as the CG, participants in this group individually perform a supervised functional activity‐based exercise protocol led by a physiotherapist/researcher.

### Intervention

2.5

The protocol was developed by experienced physiotherapists specialised in the care of patients with rheumatic diseases, with consultation from a medical specialist in SSc. It is structured based on movements commonly used in activities of daily living (Papelard et al. 2019). The intervention lasts 10 weeks, with individual sessions held twice a week at the Physiotherapy Clinic of UFPE.

Each session is divided into three phases:Mobility phase—includes range‐of‐motion exercises (diagonal trunk flexion, wrist rotation, hip and knee flexion and trunk rotation) to begin the session gently. These exercises are carried out in the same manner throughout the entire intervention period.Warm‐up phase—includes upper limb cycling for 2 minutes and lower limb cycling for 4 minutes, performed throughout the entire intervention period.Functional activity‐based exercises—include pelvic lifts, upper limb mobility, trunk diagonals, sit‐to‐stand, step‐ups and step‐downs, walking circuits, and hand strengthening and mobility exercises. These exercises are divided into movements with progressive levels of complexity and load, thus aiming to approximate the training conditions to daily life activities.

Exercise difficulty progresses over the course of the intervention. The first week focuses on introducing the movements. From the second week onward, the protocol is organised into three blocks of 3 weeks each, with exercises progressing gradually within each block.

The full protocol is available in the Supporting Information S1 of this article.

## Outcomes and Measures

3

### Feasibility Assessment

3.1

To assess the feasibility of the study, the following data will be collected (Pearson et al. 2020):Eligibility rate: the percentage of patients registered at the outpatient clinic who were eligible for recruitment;Recruitment rate: the proportion of eligible individuals who agree to participate. The number of participants recruited per month will also be estimated;Randomisation rate: the proportion of recruited participants who were successfully randomised;Retention rate: the proportion of participants who completed all planned assessments. A rate of 70% will be considered adequate (Teresi et al. 2022);Adherence rate: the proportion of participants who completed the entire protocol;Protocol fidelity: documented by recording any unplanned adaptations, including their reasons and types;Acceptability: assessed through participants' self‐reported difficulties or discomfort related to the protocol and the study. These reports will be collected as notes during each session. Acceptability will also be explored through qualitative data from semi‐structured interviews, focusing on participants' opinions and challenges during protocol implementation.

### Study Measures

3.2

Disability level is assessed using the Scleroderma Health Assessment Questionnaire (SHAQ) (Pope 2011), in which higher scores indicate greater disability. SHAQ is validated for Brazilian Portuguese (Rocha et al. 2014). In addition, lower limb physical performance is evaluated through the 30‐s sit‐to‐stand test (30sSTS) (de Santana et al. 2014) and the 6‐min walk test (6MWT), a valid and reproducible measure of functional capacity in patients with systemic sclerosis (Pugnet et al. 2018); and handgrip strength is assessed using manual dynamometry with a Jamar dynamometer, following the procedures described by Mathiowetz et al. 1984; (Mathiowetz et al. 1984).

The following outcomes were assessed using questionnaires validated for Brazilian Portuguese, with adequate psychometric properties: fatigue severity using the Fatigue Severity Scale (FSS) (Krupp et al. 1989; Mendes et al. 2008); upper limb disability using the Cochin Hand Functional Scale (CHFS) (Chiari et al. 2011; Poole 2011); symptoms of anxiety and depression using the Hospital Anxiety and Depression Scale (HADS) (Botega et al. 1995; Zigmond and Snaith 1983); resilience using the Connor‐Davidson Resilience Scale (CD‐RISC‐10) (Campbell‐Sills and Stein 2007; Solano et al. 2016); and perceived changes following the intervention using the Patient Global Impression of Change (PGIC) (Domingues and Cruz 2011; Guy and National Institute of Mental Health, Psychopharmacology Research Branch and Early Clinical Drug Evaluation Program 1979).

### Data Collection Procedures

3.3

Table 1 summarises the study phases and procedures. First, sociodemographic and clinical data are collected. Then, data related to the study outcomes are obtained.

**TABLE 1 msc70217-tbl-0001:** Study procedures.

Procedures	Enrolment	Post‐randomisation	Intervention (Weeks 1–10)	Close‐out
Enrolment				
Eligibility screening	X			
Informed consent	X			
Randomisation		X		
Intervention or control				
Intervention^a^			X	
Control^b^			X	
Assessment				
Disability‐related questionnaires		X		X
Physical tests		X		X
Semi‐structured interview		X		X

^a^
Functional activity‐based exercise protocol administered twice weekly for 10 weeks.

^b^
Usual care.

After that, the participant takes part in a semi‐structured interview. They are informed that the audio is recorded solely for transcription purposes and that their identity is protected at all times. Examiner A conducts the interview using a predefined script. However, it encourages the participant to speak freely, with no restrictions on time or content, ensuring that all opinions and reflections are thoroughly recorded. The interview is divided into two phases: a pre‐intervention component conducted at baseline to assess participants' expectations regarding the intervention, and a post‐intervention component conducted after completion of the protocol to explore participants' perceptions of the intervention.

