### Sample Size

3.4

Because the purpose of this study was to assess feasibility rather than the effectiveness of an intervention, no formal sample size calculation was performed. However, a recruitment target of 12 participants per group was established, as previously recommended (Julious 2005).

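### Examiner A is both a blinded outcome assessor and the interviewer on the intervention, so the blinding statements cannot all hold as written

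*Protocol article*

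**What the plan says.** Section 2.3 of the protocol article makes three statements on blinding:

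- on the assessors: "Data collection was performed by Examiner A or B, both of whom were blinded to group allocation";
- on the safeguard: "Participants are instructed not to disclose to researchers A and B the group to which they were allocated";
- on who knows the allocation: "The exercise protocol was administered by Examiner C, who will be the only one aware of the participants' group assignments".

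The same section has the envelopes opened only once the baseline assessment is done.

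Section 3.3 (Data Collection Procedures) puts the outcome measurements first and the semi-structured interview after them. On the interview it says "Examiner A conducts the interview using a predefined script" and that "it encourages the participant to speak freely, with no restrictions on time or content". There are two interviews. The first, at baseline, concerns expectations. The second is "a post‐intervention component conducted after completion of the protocol" and concerns how participants perceived the intervention. Section 3.1 uses the interviews as a source for acceptability, including difficulties met while following the protocol.

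Table 1 in section 3.3 lists the questionnaires, the physical tests and the first interview in the Post-randomisation column.

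**The concern.** Participants are asked to do two incompatible things with the same person: hide their group from Examiner A, and talk to Examiner A without restriction about the intervention. An honest answer to the second request breaks the first.

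The 30-s sit-to-stand test, the 6-min walk test and handgrip dynamometry are at stake. They depend on the examiner's instruction and encouragement, and they feed the ANCOVA and Cohen's d planned in section 3.6. An assessor who knows the arm could shift them, most plausibly in favour of exercise. The study is also meant to try out methods for a later full trial. A role plan that conflicts with its own blinding statement would be carried forward and reported as blinded assessment.

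**Working it through.** The plan states no figure on this point, so the check is mainly a comparison of texts, with one short calculation to bound a secondary route.

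**1. Does the interview reveal the arm?** Under sections 2.4 and 2.5, the exercise group receives the booklet (or video) plus individual supervised sessions twice a week for 10 weeks, that is 10 × 2 = 20 sessions. The control group receives the booklet or video alone. A free conversation about the intervention and its difficulties cannot hide which of these took place. If controls were not interviewed at close-out, the interview itself would show the arm. Either way, A knows the group by the end of the closing interview.

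**2. Can the statements hold together?** Once A has done the first closing interview, A is no longer blinded to that participant, C is no longer the only person aware, and the instruction not to disclose has been overridden. No section names another interviewer, and none restricts A's interviews to participants whom B assessed.

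**3. Does A learn the arm before measuring?**

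- *Closing interview, same participant.* Section 3.3 places it after the outcome measurements. If that order is kept, that participant's close-out results are already recorded. The order is given as a description of the visit, however, and not as a blinding safeguard. Nothing requires the forms to be complete first.
- *First interview.* Two readings are open. Section 2.3 opens the envelope after the baseline assessment, and section 3.3 calls the first interview a baseline, pre-intervention component. If the interview counts as part of that assessment, neither participant nor A knows the arm. Table 1, however, puts the baseline assessments and the first interview under Post-randomisation. If the participant already knows the arm at that interview, A can learn it before the 10-week intervention and hence before the close-out physical tests.
- *Other participants in the same block.* Section 2.3 says "Randomisation uses block allocation" with n = 10, and section 3.4 says "a recruitment target of 12 participants per group was established", so 24 in all.

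**4. Bound on the block route.** Assume 5:5 allocation within each block (the article gives only the size). Assume also that A knows the block boundaries and order, and that every earlier member of a block has been interviewed before the later one is tested. An allocation is then certain only when all five places of one arm have been used, so the number determined equals the length of the final run of one arm. With m = 5 per arm, its mean is

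2m/(m + 1) = 10/6 = 1.67 of 10.

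Enumerating all 252 arrangements of a 5:5 block gives the same 1.67. With 24 participants there are two full blocks and four places of a third. In those four places at most three allocations precede any participant, so five of one arm cannot have been used and nothing is determined. The total is 2 × 1.67 = 3.33 of 24, or 3.33/24 = 14%. This is an upper case: a dropout with no closing interview, or an assessment out of sequence, lowers it. Short of certainty, A's knowledge of earlier members can only improve a guess.

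**The case against.** The strongest reply is the order of the visit. If outcomes are always recorded before the interview, A is mostly unmasked after the measurement that matters. This stands for each participant's own closing visit. A reader might infer that every participant A interviews is also assessed by an unblinded examiner; the documents do not support that. It does not rescue the statements that A is blinded and that C alone knows, and it does not settle the first interview.

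A second reply is that the envelope rule in section 2.3 keeps the baseline interview blind. That is a fair reading, and Table 1 may be loosely labelled. Early unmasking is therefore conditional: the documents leave it open but do not establish it.

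Third, a reader might infer that the fixed block of 10 lets A work out the rest of a block after each interview, so that the block scheme must change. The figures do not bear this out. Certainty is confined to about 3.3 of 24 participants under favourable assumptions. Once the interviewer no longer tests anyone and does not pass information on, the inference does not reach the assessor at all.

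Fourth, the consequences are modest for this study. Section 3.6 says the analyses do not aim at definitive treatment effects. The feasibility outcomes in section 3.1 do not depend on a blinded tester. SHAQ, FSS, CHFS, HADS, CD-RISC-10 and PGIC are completed by participants who know their arm in any case. All of this stands, and it limits the severity.

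**Conclusion.** The contradiction is real and rests on the text alone: an open interview by A about the intervention is incompatible with A being blinded and C being the only person aware. The possible bias is confined mainly to three examiner-dependent tests. It arises through the first interview (only if participants know their arm by then), through a departure from the tests-before-interview order, or, to a limited extent, through knowledge of earlier block members. The documents give no basis for sizing the bias in the effect estimates, and none is claimed.

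This is a should-fix. The blinding claim is wrong as written and easily made true, but the study's main feasibility results do not depend on it.

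**What to change.** Three changes, using the existing staff:

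1. **Split the roles.** Examiner B does all questionnaires and physical tests at both visits and remains unaware of allocation. Examiner A does the interviews only, each after B's forms for that visit are complete, and does not share with B what is learned.
2. **Correct the statement on who knows.** Section 2.3 should say that C knows the allocation, that A may learn it through the interviews, and that B does not know it. The instruction not to disclose then applies to B.
3. **Reconcile Table 1 with section 2.3.** Show the baseline assessment and the expectations interview as taking place before the envelope is opened.

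The cost is a few sentences and a relabelled table, with no new staff. It also gives each participant the same rater at both visits. The downside is that B must be available for every assessment.

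The Results section (section 4) describes screening as the next phase, while the abstract calls recruitment ongoing. If anyone has already been enrolled, the split should apply from now on, with a record of who assessed and interviewed the earlier participants. No change to the block size is needed for this point.
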